#### Collection of Adverse Events

At each visit all adverse events will be documented, including the following solicited local reactions at the injection site: swelling, redness/discoloration, and pain/limitation of limb movement.

The largest diameter through the injection site of any local redness/discoloration will be recorded in millimetres. The largest diameter through the injection site of local swelling will

be recorded in millimetres. Severity of these local findings will be graded using the scales below:

Grading for swelling

| Grade | Diameter [mm] |
|-------|---------------|
| 0     | 0             |
| 1     | < 20          |
| 2     | 20 – 50       |
| 3     | > 50          |

Grading for redness/discoloration

| Grade | Diameter [mm] |
|-------|---------------|
| 0     | 0             |
| 1     | < 50          |
| 2     | 50 – 100      |
| 3     | > 100         |

If able to be ascertained in the infant, the presence and severity of local pain/limitation of limb movement at the site of vaccination will be determined using the following scale:

| Grade | Description                                          |
|-------|------------------------------------------------------|
| 0     | No pain at all                                       |
| 1     | Painful on touch, no restriction in movement of limb |
| 2     | Painful when limb is moved                           |
| 3     | Unable to use limb due to pain                       |

Adverse events will only be recorded in the CRF if they occurred up to 30 days post vaccination, unless they meet the criteria for serious adverse event as outlined above. Serious adverse events will be collected throughout the study period.

Episodes of malaria detected as endpoints in the efficacy evaluation will not be reported as Adverse Events.

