## **Endpoints for the Phase 2b Trial**

### ***Safety endpoints***

SAEs occurring from first vaccination until the end of the study

Local and systemic solicited and unsolicited adverse events, considered possibly, probably, or definitely related to vaccination, occurring from first vaccination until 1 month post second vaccination (study day 93).

Solicited injection site adverse events are pain/limitation of limb movement, swelling and redness/discoloration. Solicited systemic adverse events are fever, loss of appetite, irritability, and drowsiness.

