### **Administration of study vaccines**

For Group A, vaccination on Day 0 is with ChAd63 ME-TRAP, and vaccination on Day 56 is with MVA ME-TRAP. The staff administering the vaccine may both prepare the vaccine in the administration syringe and administer it.

For the Phase 2 Trial, vaccination on Day 0 is with ChAd63 ME-TRAP (Group B) or Rabies Vaccine (Group C), and vaccination on Day 56 is with MVA ME-TRAP (Group B) or Rabies Vaccine (Group C). The staff responsible for the storage and preparation of study vaccines will be aware of Group allocation, and will prepare the vaccine in the administration syringe accordingly. They will mask the contents of the administration syringe with an opaque label to ensure that the parent(s)/guardian(s), the staff administering the vaccine, and all other staff, remain blinded to the Group allocation of the study participant. The staff responsible for the storage and preparation of the vaccines will play no other role in the study, so that blinding is maintained.

Vaccinations will be administered intramuscularly into the anterolateral thigh. The same side will be used for both vaccinations.

ChAd63 ME-TRAP and MVA ME-TRAP are genetically modified organisms. In order to minimise dissemination of the recombinant vectored vaccine viruses into the environment, the inoculation site for all vaccinations will be covered with a dressing after immunisation. This should absorb any virus that may leak out through the needle track, and will be removed from the injection site after 30 minutes. Vaccine administrators will follow precautions for the safe handling of GMOs (including the use of eye protection and gloves).

Each volunteer will be monitored for one hour (or longer if necessary) after each vaccination. Resuscitation (including intubation) equipment and medication will be available in the clinic site and a clinician trained in resuscitation will be present at all times during this immunisation time period.

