### ***Safety analyses***

Assessment of the safety and reactogenicity of vaccinations will be undertaken by summary listing of all solicited and unsolicited local and systemic adverse events (including results of clinical laboratory investigations where deemed adverse events), considered possibly, probably, or definitely related to vaccination; and line listing of all SAEs.

Safety endpoints will be summarised for Group B and C. The number and percentage of patients in each group who have any local reaction will be compared (using the chi-squared test, and by calculating confidence intervals on differences in percentages). Similarly, the numbers who have any systemic reaction or SAE will be compared between groups. Analysis will also be carried out according to vaccine received.

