### Grading the severity of adverse events

For adverse events other than local swelling, redness/discoloration and pain/limitation of limb movement, for which the severity scales are detailed above, AEs will be graded according to the DAIDS AE grading table, published in 2004. The DAIDS AE grading table classifies adverse events into one of four grades, ranging from mild to potentially life-threatening. The DAIDS AE grading table has indications for each of over sixty clinical parameters and forty laboratory parameters for grading adult and paediatric AEs. The table also includes general guidelines for estimating the grade of parameters not explicitly listed. Each grade is described broadly below:

- Grade 1 (mild): awareness of a symptom, but the symptom is easily tolerated and causes no or minimal interference with usual activity.
- Grade 2 (moderate): discomfort enough to cause greater than minimal interference with usual activity.
- Grade 3 (severe): incapacitating; symptoms causing inability to perform usual activities; requires absenteeism or bed rest.
- Grade 4 (potentially life-threatening): symptoms causing inability to perform basic self-care functions OR medical or operative intervention is indicated to prevent permanent impairment, persistent disability or death.

The DAIDS AE grading scales for the solicited adverse events of fever and of loss of appetite (anorexia) are shown below,

Grading for fever

| Grade | Temperature (nonaxillary) |
|-------|---------------------------|
| 1     | 37.7-38.6 °C              |
| 2     | 38.7-39.3 °C              |
| 3     | 39.4-40.5 °C              |
| 4     | >40.5 °C                  |

Grading for loss of appetite

| Grade | Description                                                                                                              |
|-------|--------------------------------------------------------------------------------------------------------------------------|
| 1     | Loss of appetite without decreased oral intake                                                                           |
| 2     | Loss of appetite associated with decreased oral intake without significant weight loss                                   |
| 3     | Loss of appetite associated with significant weight loss                                                                 |

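### The 30-day limit on recording non-serious adverse events contradicts the continuous safety endpoint to Day 93, and that endpoint keeps only events judged related

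*Protocol*

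**What the plan says.** **Recording rule.** Section 10, Collection of Adverse Events: "Adverse events will only be recorded in the CRF if they occurred up to 30 days post vaccination". SAEs are exempt: "Serious adverse events will be collected throughout the study period".

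**Endpoint.** Section 5, Safety endpoints (repeated in the Section 1 synopsis), has two parts. The serious part is "SAEs occurring from first vaccination until the end of the study". The non-serious part is "Local and systemic solicited and unsolicited adverse events, considered possibly, probably, or definitely related to vaccination", and its period is "occurring from first vaccination until 1 month post second vaccination (study day 93". No break between the two vaccinations is stated.

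**Schedule.** Under Administration of study vaccines (Section 7), the first Phase 2b vaccination is on Day 0 and "vaccination on Day 56 is with MVA ME-TRAP (Group B) or Rabies Vaccine (Group C". Table 1 allows ±14 days for the Day 56 visit and marks recording of solicited and unsolicited AEs at every visit from Day 0 to Day 93. The Day 56 text in Section 8 has the AE records updated at that visit. Section 10 itself also requires all AEs to be documented at each visit. The Day 93 window is ±2 days in Table 1 and ±14 days in Table 3.

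**Analysis.** Section 9, Safety analyses, lists non-serious events "considered possibly, probably, or definitely related to vaccination; and line listing of all SAEs". It then compares Groups B and C on the numbers of children with any local reaction, and with any systemic reaction or SAE.

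**Fever grading.** The Section 10 grading table is headed "Temperature (nonaxillary").

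**The concern.** An endpoint period and the recording rule that feeds it should cover the same days. Here the rule appears to stop 30 days after the first vaccination and restart at the second, while the endpoint runs straight through. Section 11 makes the case report form (CRF) the source document, so a non-serious event left off it may exist nowhere else, and no later analysis plan could recover it. The mismatch is visible elsewhere too: Section 8 (Data collection) captures antipyretics, analgesics and systemic antibiotics, with indication, continuously from dose 1 to one month after dose 2. A treated illness on Day 40 would have its drug recorded but not the event. The rule is not confined to Groups B and C, so it also bears on the Group A safety data to Day 63 that the DSMB reviews before the second Group B and C vaccination.

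The second issue is what is kept. The trial has a blinded randomised control arm, which allows a comparison of AE frequency that needs no causality judgement. Restricting the non-serious endpoint to events judged related gives up that comparison for unsolicited events judged unrelated.

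**Working it through.** **1. The plan's own figure.** The protocol equates one month after the second vaccination with Day 93. From Day 56: 56 + 28 = 84, 56 + 30 = 86, 56 + 31 = 87. None is 93. In fact 93 - 56 = 37 days, while 93 - 63 = 30, so Day 93 is 30 days after the Day 63 visit. With the second vaccination anywhere in its Day 42-70 window, Day 93 lies between 93 - 70 = 23 and 93 - 42 = 51 days after it.

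**2. Days covered.** Endpoint days are 0 to 93, which is 94 days. If the rule means 30 days after each vaccination, recorded days are 0-30 and v to v + 30, where v is the day of the second vaccination.

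| v | Unrecorded before v | Unrecorded after v | Total of 94 |
|---|---|---|---|
| 42 | 31-41 (11) | 73-93 (21) | 32 (34.0%) |
| 49 | 31-48 (18) | 80-93 (14) | 32 (34.0%) |
| 56 | 31-55 (25) | 87-93 (7) | 32 (34.0%) |
| 63 | 31-62 (32) | none | 32 (34.0%) |
| 70 | 31-69 (39) | none | 39 (41.5%) |

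Up to v = 63 both 31-day blocks fit inside the endpoint period, so 94 - 62 = 32. At v = 70 the second block runs to Day 100 and only 24 of its days (70-93) count: 94 - 31 - 24 = 39.

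**3. From days to children (assumption).** The documents give no AE rate. If a proportion p of children had a non-serious event over the 94 days at a constant rate, the proportion with one recorded at v = 56 would be 1 - (1 - p)^(62/94). For p = 10%, 30%, 50% and 80% this gives 6.7%, 21%, 37% and 65%. Vaccine reactions cluster soon after injection, inside the recorded blocks, so for those the loss is smaller than this.

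**4. The Day 93 visit.** ±2 places it on Days 91-95; ±14 places it on Days 79-107. The two tables therefore disagree on when AE collection may end.

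**5. Relatedness.**

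| Item | Causality filter stated? | Group comparison stated? |
|---|---|---|
| SAEs | No | Yes |
| Any local reaction | No | Yes |
| Any systemic reaction | No | Yes |
| Non-serious AE endpoint and listing | Yes, related only | Summary by group |
| Non-serious unsolicited events judged unrelated | Excluded | None |

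**The case against.** The strongest reply is that this is a drafting conflict, not a data loss. Three other places point to continuous recording: the Section 10 sentence on documenting all AEs at each visit, the AE row of Table 1, and the Day 56 update in Section 8. A site following those would record everything the endpoint needs. One could also read the 30 days as running from the completed course, in which case only the days after v in the table are lost (7 on schedule, none from Day 63 onward). Both replies stand to this extent: events are lost only if the Section 10 limit prevails and is applied per vaccination. They do not remove the conflict, because that sentence is the one worded as a restriction on the CRF.

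It is also fair that 34% counts days, not events. The home and clinic visits on Days 1-3, 7, 57-59 and 63 all fall inside the recorded blocks when vaccination is on schedule, as do the Day 21 and Day 63 laboratory tests. The rule is the same in both blinded arms, so by itself it costs counts and precision and favours neither.

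Three stronger readings are tempting and are not supported:

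- That the whole harm comparison is limited to related events. The Section 9 comparison sentences carry no relatedness filter, and SAEs are compared whatever their cause.
- That the harm comparison is under-counted, or the endpoint cannot be produced. Either follows only if the Section 10 limit overrides the schedule.
- That axillary readings just above 37.5°C are fevers without a grade. That threshold serves blood films, malaria case definitions and the vaccination contraindication; it is never defined as the threshold for the solicited fever AE.

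**Conclusion.** The contradiction is real and should be resolved before AE data are collected. If the limit is applied literally after each vaccination, 32 of 94 endpoint days (34%) go unrecorded for non-serious AEs for a second vaccination on Days 42-63, rising to 39 (41.5%) at Day 70. The consequence is lost late-onset non-serious events, equally in both arms; SAEs are fully captured. The stated end day is wrong by the protocol's own schedule (37 days, not one month), and its visit window differs between Tables 1 and 3.

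The relatedness point is separate and narrower: non-serious unsolicited events judged unrelated have no stated between-group comparison. A statistical analysis plan could add one, but only for events that were recorded.

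The fever table needs only a clarification. It grades nonaxillary temperatures, the protocol's other temperature thresholds are axillary, and the route for AE temperatures is not stated.

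**What to change.** - Delete the 30-day CRF limit in Section 10. Record all AEs continuously from first vaccination to the later of the Day 93 visit or 30 days after the actual second vaccination. Stopping at the Day 93 visit alone would not do: a child vaccinated on Day 70 would have about 23 days of follow-up, fewer than the present rule gives (to Day 100).
- Restate the endpoint period in Sections 1 and 5 to match, correct the equation of Day 93 with one month, and reconcile the Day 93 window between Tables 1 and 3.
- In Section 9, compare all AEs between Groups B and C regardless of causality, with related events as a subset.
- State the measurement route for AE temperatures and reconcile it with the nonaxillary grading table.

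The cost is wording, a CRF instruction and somewhat more AE entries, mainly between Days 31 and 55. For second vaccinations after Day 63 the 30-day mark falls on Days 94-100. Those last days could be covered by asking about AEs at the Day 123 home visit, which is already scheduled.

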#### Follow-up of Adverse Events

All AEs will be followed until resolution of the signs or symptoms or laboratory changes occurs, or until a non-study related causality is assigned.

Subjects who have moderate or severe on-going adverse events at the completion of the study will be advised to consult a physician if the event is not considered to be related to the study vaccine. A follow-up visit will be arranged to manage the problem and to determine the severity and duration of the event, if it is considered to be related to the study vaccine. If appropriate, specialist review will be arranged by CNRFP investigators.

Any serious adverse event possibly related to the vaccine and occurring after trial termination should be reported by the investigator according to the procedure described below.

#### Reporting of Adverse Events

Every SAE occurring throughout the trial must be reported by telephone, email or fax to the sponsor, LSM and DSMB by the investigator as soon as (s)he is alerted of it and within one working day, even if the investigator considers that the adverse event is not related to vaccination. The investigator will then complete a SAE report form as soon as possible and within five working days or seven calendar days.

Any relevant information concerning the adverse event that becomes available after the SAE report form has been sent (outcome, precise description of medical history, results of the investigation, copy of hospitalisation report, etc.) will be forwarded to the Sponsor in a timely manner. The anonymity of the subjects shall be respected when forwarding this information.

SAEs that are suspected to be related to the vaccine will be reported to the Ethics Committee within 15 calendar days of the site becoming aware of the event. If the event is fatal or life-threatening, the event will be reported within 7 calendar days.

Suspected unexpected serious adverse reactions (SUSARs) will be reported according to national regulatory guidelines. The sponsor pledges to inform the Authorities of any trial discontinuation and specify the reason for discontinuation.

The causal relationship between the AE and the product will be evaluated by the investigator. This interpretation will be based on the type of event, the relationship of the event to the time of vaccine administration, and the known biology of vaccine therapy. The following are guidelines for assessing the causal relationship:

No relationship:

No temporal relationship to study product; and

Alternate aetiology (clinical state, environmental or other interventions); and

Does not follow known pattern of response to study product

Unlikely relationship

Unlikely temporal relationship to study product; and

Alternate aetiology likely (clinical state, environmental or other interventions); and

Does not follow known typical or plausible pattern of response to study product

Possible relationship:

Reasonable temporal relationship to study product; or

Event not readily produced by clinical state, environmental or other interventions; or

Similar pattern of response to that seen with other vaccines

Probable relationship:

Reasonable temporal relationship to study product; and

Event not readily produced by clinical state, environment, or other interventions or

Known pattern of response seen with other vaccines

Definite relationship:

Reasonable temporal relationship to study product; and

Event not readily produced by clinical state, environment, or other interventions; and

Known pattern of response seen with other vaccines

### Grading the severity of adverse events

For adverse events other than local swelling, redness/discoloration and pain/limitation of limb movement, for which the severity scales are detailed above, AEs will be graded according to the DAIDS AE grading table, published in 2004. The DAIDS AE grading table classifies adverse events into one of four grades, ranging from mild to potentially life-threatening. The DAIDS AE grading table has indications for each of over sixty clinical parameters and forty laboratory parameters for grading adult and paediatric AEs. The table also includes general guidelines for estimating the grade of parameters not explicitly listed. Each grade is described broadly below:

- Grade 1 (mild): awareness of a symptom, but the symptom is easily tolerated and causes no or minimal interference with usual activity.
- Grade 2 (moderate): discomfort enough to cause greater than minimal interference with usual activity.
- Grade 3 (severe): incapacitating; symptoms causing inability to perform usual activities; requires absenteeism or bed rest.
- Grade 4 (potentially life-threatening): symptoms causing inability to perform basic self-care functions OR medical or operative intervention is indicated to prevent permanent impairment, persistent disability or death.

The DAIDS AE grading scales for the solicited adverse events of fever and of loss of appetite (anorexia) are shown below,

Grading for fever

| Grade | Temperature (nonaxillary) |
|-------|---------------------------|
| 1     | 37.7-38.6 °C              |
| 2     | 38.7-39.3 °C              |
| 3     | 39.4-40.5 °C              |
| 4     | >40.5 °C                  |

Grading for loss of appetite

| Grade | Description                                                                                                              |
|-------|--------------------------------------------------------------------------------------------------------------------------|
| 1     | Loss of appetite without decreased oral intake                                                                           |
| 2     | Loss of appetite associated with decreased oral intake without significant weight loss                                   |
| 3     | Loss of appetite associated with significant weight loss                                                                 |
| 4     | Life threatening consequences OR Aggressive intervention indicated [eg, tube feeding or total parenteral nutrition(TPN)] |

Laboratory tests will also be graded on the DAIDS AE grading table.

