| Review contraindications to vaccination                                                                 |             | X                                |            |       |        | X                     |             |       |     |                     |      |                          |      |                                                       |      |
| Recording of concomitant medication                                                                     | X           | X                                | X          | X     | X      | X                     | X           | X     | X   | X                   | X    | X                        | X    | X                                                     | X    |
| Recording of solicited and unsolicited adverse events                                                   |             | X                                | X          | X     | X      | X                     | X           | X     | X   |                     |      |                          |      |                                                       |      |
| Recording of SAEs                                                                                       |             | X                                | X          | X     | X      | X                     | X           | X     | X   | X                   | X    | X                        | X    | X                                                     | X    |
| Blood Film for P. falciparum                                                                     | X           |                                  |            | X     |        | X                     |             | X     |     |                     | X    |                          | X    |                                                       | X*   |
| Blood Film for P. falciparum if axillary temp ≥37.5 and/or history of fever within last 24 hours |             | X                                | X          | X     | X      | X                     | X           |       | X   | X                   |      | X                        |      | X                                                     |      |

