### **Contraindications to vaccine administration**

The following constitute contraindications to administration of vaccine at that point in time. If any one of these occurs at the time scheduled for vaccination, the subject may be

vaccinated at a later date or withdrawn, at the discretion of the Principal Investigator. Medical care including inpatient care if necessary will be offered.

- Acute disease at the time of vaccination. Acute disease is defined as the presence of a moderate or severe illness with or without fever. All vaccines can be administered to persons with a minor illness at the discretion of the investigators. Details of any minor illness will be recorded in the CRF.
- Axillary temperature of  $\geq 37.5^{\circ}\text{C}$  ( $99.5^{\circ}\text{F}$ ) at the time of vaccination.
- Receipt of routine EPI vaccination within one week of study vaccine

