### **Day 7**

Medical history, temperature monitoring +/- physical examination will be performed. The CRF will be updated, including the records of AEs and concomitant medications.

If axillary temperature  $\geq 37.5^{\circ}\text{C}$  and/or History of fever within the last 24 hours, a blood smear will be obtained for malaria diagnosis.

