#### **Case Detection for Clinical *P. falciparum* malaria**

For the primary efficacy endpoint, passive case detection will be used and will consist of continuous availability of medical care at the trial site and at the community clinics to which trials participant villages belongs to.

All subjects presenting to health facilities in the study area will be evaluated as potential cases of clinical malaria disease. A blood sample for the evaluation of malaria parasites will be taken for all children who are reported to have had a fever within 24 hours of presentation or have a measured axillary temperature of  $\geq 37.5^{\circ}\text{C}$ . A *P. falciparum* rapid diagnosis test will be performed to guide immediate patient management. However, efficacy results will be based on blood slide reading. The research team will be available 24 hours/ day, 7 days a week. The participants' parents/guardians will be informed to bring the child to the health facility should the child be "unwell".

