#### **Safety follow-up**

Trained field workers under the supervision of the investigators will visit daily each enrolled child for days 1 to 3 post vaccination. If necessary the child will continue to be seen by the field worker on subsequent days for follow-up of adverse events. The field workers will visit the child at 30 day intervals as indicated on the Timeline of Study Visits (Table 1). In the event that the field worker finds any Grade 3 solicited general or unsolicited symptoms, the volunteer will be brought to the vaccination centre for examination by a study clinician. During the field worker visits, the children's parent(s)/guardian(s) will be asked retrospectively if any medical event that might be a SAE occurred since the last visit and this information will be recorded. Unreported SAEs detected in this way will be investigated and reported by the PI or delegate on the corresponding SAE.

If a study participant is reported to be unwell at the time of a visit, the field worker will advise the parents to report to the trial site clinic or the nearest health facility where a study nurse will be posted and will notify this referral to the clinical team for follow up. In the event that a study participant is seriously ill, the field worker will inform the PI or designate, and transport will be arranged, to the referral hospital (where a study physician is posted), if judged appropriate by the responsible clinician.

In case a study participant is unwell and referred to the trial site clinic or health facility, a duplicate blood film will be obtained should the volunteer present symptoms or signs compatible with malaria (axillary temperature  $\geq 37.5^{\circ}\text{C}$ , History of fever within the last 24 hours, loss of appetite, malaise, vomiting and diarrhoea etc).

A study clinician will review the infant at the Clinic Visits, on Days 7, 21, 56, 63, 93, 243, 363, and 723, for full safety and reactogenicity assessment.

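### Solicited fever is graded on a non-axillary scale, while the axilla is the only measuring site the protocol names, and nothing links the two

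*Protocol*

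**What the plan says.** Section 5 (Safety endpoints) lists fever as a solicited event without a cut-off or a measuring site: "Solicited systemic adverse events are fever, loss of appetite, irritability, and drowsiness". The lead-in endpoints use the same list.

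Section 10 (Grading the severity of adverse events) supplies the scale: "The DAIDS AE grading scales for the solicited adverse events of fever and of loss of appetite (anorexia) are shown below". The temperature column of the fever table is headed "Temperature (nonaxillary". Its bands are 37.7–38.6 °C (Grade 1), 38.7–39.3 °C (Grade 2), 39.4–40.5 °C (Grade 3) and above 40.5 °C (Grade 4).

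Elsewhere, each trial temperature that has a stated site is axillary with a cut-off of 37.5 °C:

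- the malaria case definitions in Section 5 (Efficacy Endpoints);
- the contraindication to vaccination in Section 7;
- the blood-film row in Tables 1 and 3, "if axillary temp ≥37.5 and/or history of fever within last 24 hours", and the matching text for Days 7, 21, 56, 63 and 93;
- case detection in Section 8, where a child may "have a measured axillary temperature of" 37.5 °C or more;
- the symptom list in Section 8 (Safety follow-up).

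The clinic-visit text gives no site for the routine reading: "Medical history, temperature monitoring +/- physical examination will be performed".

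The grade has a direct use in Section 8 (Safety follow-up). If the field worker "finds any Grade 3 solicited general or unsolicited symptoms, the volunteer will be brought to the vaccination centre", a study clinician examines the child there.

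**The concern.** The scale and the measurement do not match. The scale is labelled as not meant for axillary readings, yet the axilla is the only site the protocol ever specifies. Staff at the post-vaccination visits will most likely hold an axillary reading and a non-axillary table, with no instruction for getting from one to the other.

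Three things depend on the grade or on whether a reading counts as fever:

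- the description of how severe post-vaccination fever was, in all groups;
- the Group A safety data to Day 21 and to Day 63, which come from 30 children without a control group and which the DSMB reviews before each Group B and C vaccination;
- the Grade 3 trigger for examination by a study clinician.

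A later analysis plan cannot repair this. Site and scale are applied by field staff at the visit, and a site that was not recorded cannot be recovered afterwards.

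**Working it through.** **1. Is the site at the key visits really axillary?** The text for Days 1–3 and 57–59 says only that adverse events are assessed and recorded. However, Table 1 marks the axillary blood-film row for visits 2–4 and 8–10, which are those home visits. So the only temperature specified at the visits where most reactogenicity will be seen is axillary. No part of the protocol schedules a reading at another site or gives a conversion or an axillary scale.

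**2. What follows without any outside figure?** Apply the Section 10 bands as printed to readings in 0.1 °C steps from the 37.5 °C cut-off upward. Grade 1 begins at 37.7 °C, so exactly two readings have no grade: 37.5 and 37.6 °C. An axillary reading at either value prompts a blood film and contraindicates vaccination on that day, but does not reach Grade 1.

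**3. What follows if axillary readings run lower?** The documents give no axillary-to-non-axillary difference, so the offset d is an assumption, shown from 0 to 1.0 °C. For each axillary reading t from 37.5 to 41.0 °C (36 values), compare grade(t), as recorded, with grade(t + d), as it would be after conversion. The axillary reading at which Grade 3 would start is 39.4 − d.

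| Assumed d (°C) | Readings of 36 that would move up at least one grade | Grade 3 would start at axillary (°C) |
|---|---|---|
| 0 | 0 | 39.4 |
| 0.2 | 8 | 39.2 |
| 0.3 | 11 | 39.1 |
| 0.5 | 17 | 38.9 |
| 0.8 | 25 | 38.6 |
| 1.0 | 29 | 38.4 |

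Example at d = 0.5: axillary 38.9–39.3 °C corresponds to 39.4–39.8 °C, which is Grade 3, but is recorded as Grade 2. The 17 readings are 37.5–37.6 (2 values, ungraded instead of Grade 1), 38.2–38.6 (5, Grade 1 instead of 2), 38.9–39.3 (5, Grade 2 instead of 3) and 40.1–40.5 (5, Grade 3 instead of 4): 2 + 5 + 5 + 5 = 17.

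These are counts of points on a temperature grid, not of children. The protocol gives no distribution of fevers, so no share of participants can be derived.

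**4. Where does the grade enter the analysis?** Section 9 (Safety analyses) compares the number of children with any systemic reaction. A move between Grades 1, 2 and 3 leaves that count unchanged. Only the ungraded readings in step 2 could alter it, and only if ungraded is taken to mean not counted, which the protocol does not say.

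**The case against.** The strongest reply is that nothing in the protocol tells staff to enter axillary readings in this table. Taken literally, Section 10 calls for a non-axillary temperature, and the visit text leaves the site open. In addition, 37.5 °C is a trigger for malaria testing, a case criterion and a reason to delay vaccination. It is never given as the definition of solicited fever, and a testing threshold may legitimately differ from the bottom of a severity scale. Both points stand, and they make the under-grading conditional. They do not remove the mismatch, because a non-axillary scale with no non-axillary measurement provided for is still unusable as written.

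A reader might infer three stronger things that the documents do not support:

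- **That fevers are graded too low as a matter of fact.** This needs unconverted entry and an axillary reading that runs lower. The documents state neither, and at zero offset nothing shifts.
- **That the Group B versus C comparison is biased.** The comparison is of any systemic reaction, and both blinded arms use the same scale.
- **That a child with severe fever would be missed.** Section 8 has other routes: a child reported unwell is advised to attend the clinic or nearest facility and the clinical team is told, and a seriously ill child is reported to the principal investigator or designate. The film row in Table 1 also applies whatever the grade. The Grade 3 trigger may be weakened, but it is not the only safeguard.

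Nor does the protocol state a fever-grade rule for the DSMB's decision. The effect there is on how the data read.

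**Conclusion.** The inconsistency is real and should be corrected. The fever scale is for non-axillary temperature, every trial temperature with a named site is axillary, and nothing bridges them.

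The one result that needs no offset is the gap at 37.5 and 37.6 °C, and even that assumes axillary readings go into the table as they are. Under-grading above that is possible, but its size is unknown: none at zero offset, and from 8 to 29 of the 36 grid readings for assumed offsets of 0.2 to 1.0 °C.

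The effect falls on the absolute severity summaries, the uncontrolled Group A data reviewed by the DSMB, and the Grade 3 referral trigger. The between-group comparison of systemic reactions is affected only if ungraded readings go uncounted, and no differential effect is shown. This is a moderate point about absolute safety description. It does not threaten the efficacy analysis.

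**What to change.** State in Section 10 one measuring site for temperatures used in adverse-event grading, and apply it at every adverse-event visit, including the home visits. Use a fever grading table validated for that site. Give one definition of solicited fever and use it in both Sections 9 and 10, so that it is clear which readings count as a systemic reaction.

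Then reconcile the fever table with the blood-film row in Tables 1 and 3, the vaccination contraindication in Section 7, and case detection and Safety follow-up in Section 8. Where a testing threshold and a grading threshold are meant to differ, say so. The sponsor's safety physician should choose the thresholds; this review proposes none.

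The cost is one table and one CRF field. Fever grades may become slightly less favourable, or less directly comparable with trials that used the published bands.
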